### Sample size estimation

The primary efficacy endpoint is the change in peak VO₂ after 12 weeks of treatment. The sample size estimation was based on data from the iPOWER study (15), in which the CFVR served as the diagnostic criterion for coronary microvascular dysfunction (CMD). In participants with a CFVR ≥2.0 (non-CMD group, *n* = 22), the median peak VO₂ was 28.6 mL/kg/min (IQR: 22.1–31.7); in those with a CFVR <2.0 (CMD group, *n* = 27), the median peak VO_2_ was 17.3 mL/kg/min (IQR: 15.5–21.3). On the basis of these data, the estimated between-group difference in means was 4.71 mL/kg/min, with a pooled standard deviation of 6.5 mL/kg/min. Using a two-sided superiority design with a significance level *α* = 0.05 and a target power of 90% (1-*β* = 0.90), the required evaluable sample size per group was calculated using the formula for two-independent-sample *t*-test with equal variances:$$n=2\times {\left(\frac{Z_{1-\alpha /2}+Z_{1-\beta }}{\Delta /\sigma }\right)}^{2}$$Where $\;Z_{1-\alpha /2}$ = 1.96, $Z_{1-\beta }$  = 1.282, and *δ* = 4.71, *σ* = 6.5. This given *n* = 41.5 per group, rounded up to 42 evaluable subjects per group (total 84). The calculation was performed using PASS 2023 (NCSS, LLC, Kaysville, UT, USA), which confirmed that 42 subjects per group achieve 90.68% power under the same assumptions.

To account for an anticipated 15% attrition rate (dropout or loss to follow-up), the sample size was inflated using the formula:$$n^{\prime }=\frac{n}{1\text{-}\mathrm{DR}}$$where DR is the dropout rate. With *n* = 42 and *DR* = 0.15, *n'*=42/0.85 = 49.41, rounded up to 50 participants per group. Thus, the final target sample size is 100 participants in total (50 per group).

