#### Primary endpoints

The primary endpoint is the change in peak VO_2_ measured by CPET from baseline to week 12. The primary analysis will be performed via an analysis of covariance (ANCOVA) model, with the treatment group as a fixed effect and the corresponding baseline value as a covariate. The study center will be included either as a fixed effect or as a random effect in a mixed-effects model, depending on model fit and the distribution of participants across centers. The results are reported as adjusted mean differences with 95% confidence intervals and two-sided *P* values.

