#### Secondary outcomes

Continuous secondary outcomes—including laboratory parameters, patient-reported outcome scores, and CPET indices other than peak VO_2_—will be analyzed as changes from baseline via ANCOVA with baseline adjustment. If distributional assumptions are violated, rank-based ANCOVA or nonparametric methods (e.g., the Mann–Whitney *U*-test) will be applied. Categorical outcomes will be compared via the chi-square test or Fisher's exact test, as appropriate. Exploratory analyses will assess correlations between changes in peak VO_2_ and improvements in symptoms or quality of life (e.g., SAQ scores) via Pearson or Spearman coefficients. Safety outcomes, including adverse events, major adverse cardiovascular events, and changes in liver and renal function, will be summarized descriptively and compared between groups where applicable.

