#### Missing data

Missing primary endpoint data at week 12 will be handled via multiple imputation under the missing-at-random assumption. Sensitivity analyses will include complete-case analysis and other prespecified approaches when needed, such as pattern-mixture models or conservative imputation methods.

All the statistical tests will be two-sided. The overall two-sided significance level for the primary endpoints will be set at *α* = 0.05 after adjustment for multiplicity. Analyses will be performed via SPSS (v26.0) and/or validated statistical software (e.g., SAS/R) as specified in the SAP.

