CPET is the gold standard for evaluating functional capacity in patients with cardiovascular disease (30). In CMVD, impaired coronary microvascular vasodilation leads to a mismatch between myocardial oxygen supply and demand during physical exertion, resulting in reduced exercise tolerance (21). CPET objectively quantifies this limitation through key gas exchange parameters. Peak VO_2_ is a strong predictor of cardiovascular morbidity and mortality and has been shown to correlate with coronary microvascular function in symptomatic populations (8). In the iPOWER study, women with confirmed CMD (CFVR <2.0) had markedly lower peak VO_2_ values than asymptomatic controls with normal microvascular function, independent of age and cardiovascular risk factors (15). Other CPET-derived indices, such as oxygen pulse, ventilatory efficiency (VE/VCO_2_ slope), and heart rate recovery, provide further insight into cardiovascular and autonomic adaptation to exercise, and may reveal subclinical functional impairment even in the absence of overt ischemia (31). Given its ability to capture the physiological consequences of microvascular dysfunction, CPET is well suited for assessing treatment efficacy in CMVD trials (32). Improvement in peak VO_2_ after intervention may reflect not only better myocardial oxygen delivery but also meaningful gains in daily functional capacity and quality of life (33).

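### The exploratory correlation of change in peak VO₂ with symptom or quality-of-life improvement names no treatment arm; if arms are pooled and STDP moves both outcomes, it cannot be read as a within-arm link.

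*Protocol article*

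**What the plan says.** The analysis is one sentence in the protocol article (Statistical analysis, Secondary outcomes), which opens "Exploratory analyses will assess correlations between changes in peak VO"₂. So it is labelled exploratory. It relates the change in peak VO₂ to "improvements in symptoms or quality of life (e.g., SAQ scores) via Pearson or Spearman coefficients", and gives no further detail. The sentence does not say whether the coefficient is computed over all patients, within each arm, or with arm partialled out.

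The primary analysis, by contrast, is an ANCOVA "with the treatment group as a fixed effect and the corresponding baseline value as a covariate" (Primary endpoints). Under Missing data the article says "All the statistical tests will be two-sided" and sets a 5% level for the primary endpoints. It attaches no p-value or threshold to the correlation.

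The Discussion states of a rise in this endpoint that it "after intervention may reflect not only better myocardial oxygen delivery but also meaningful gains in daily functional capacity and quality of life". That is the kind of statement a reader would want this correlation to inform.

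**The concern.** Pearson and Spearman coefficients are two-variable statistics with no place for treatment arm. The trial is designed around a rise in peak VO₂ on STDP, and it also evaluates STDP on symptoms and quality of life. If both respond, STDP patients sit higher on both changes and placebo patients lower on both. Pooled over arms, that alone gives a positive coefficient, even if patients with a larger gain in peak VO₂ feel no better than others in their own arm.

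The coefficient then partly repeats what the between-arm analyses already show, namely that STDP affects each outcome. At stake is interpretation. A positive pooled result could be presented as evidence that gains in peak VO₂ track gains in how patients feel, when a shared arm shift explains some or all of it. Where a real positive within-arm association exists, the shift can add to it.

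**Working it through.** **Inputs from the document (Sample size estimation).** The section states that "the estimated between-group difference in means was 4.71 mL/kg/min, with a pooled standard deviation of 6.5 mL/kg/min". The standardised effect on peak VO₂ is d₁ = 4.71/6.5 = 0.725. Evaluable patients are 42 per arm (84 in total); the target is 50 per arm after 15% attrition; allocation is 1:1.

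**The plan's own figure.** The printed formula gives 2 × ((1.96 + 1.282) × 6.5/4.71)² = 40.04, against the printed 41.5. The exact two-sample t-test has 89.99% power at 41 per group and 90.68% at 42. The stated 42 and 90.68% are therefore reproduced, and 42/0.85 = 49.41 rounds up to 50.

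**Assumed.** The document gives no effect on SAQ or any other symptom scale, so d₂ is varied. Within each arm the two changes are independent normals, so the true within-arm correlation is 0.

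**Induced pooled correlation.** With 1:1 allocation the arm means contribute d₁d₂/4 to the covariance and d²/4 to each variance:

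r = (d₁d₂/4) / √[(1 + d₁²/4)(1 + d₂²/4)]

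For d₁ = d₂ = 0.725: d₁d₂/4 = 0.131, so r = 0.131/1.131 = 0.116.

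**Chance of significance, by hand.** Fisher's z for r = 0.116 is 0.1165. Multiplied by √(84 − 3) = 9 this is 1.05. The chance of exceeding 1.96 is P(Z > 0.91), about 18%.

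**Simulation.** There were 20,000 trials per scenario, with two-sided 5% tests. Pooled is the plain coefficient; adjusted is the partial correlation given arm.

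| Peak VO₂ effect (SD) | SAQ effect (SD, assumed) | Induced r | Pooled Pearson, 42/arm | Adjusted Pearson, 42/arm | Pooled Pearson, 50/arm |
|---|---|---|---|---|---|
| 0 | 0 | 0 | 5.0% | 5.0% | 5.1% |
| 0.725 | 0 | 0 | 5.1% | 5.1% | 5.1% |
| 0.725 | 0.3 | 0.05 | 7.2% | 4.9% | 8.0% |
| 0.725 | 0.5 | 0.08 | 11.4% | 4.8% | 12.6% |
| 0.725 | 0.725 | 0.12 | 18.5% | 5.0% | 21.3% |
| 0.725 | 1.0 | 0.15 | 27.9% | 5.0% | about 34% |
| 0.3 | 0.3 | 0.02 | 5.2% | 5.0% | 5.5% |
| 0.5 | 0.5 | 0.06 | 8.2% | 5.0% | 9.3% |

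Spearman is nearly identical (18.4% pooled and 4.9% adjusted at 42 per arm with both effects 0.725). Over all scenarios run, the adjusted version stays between 4.6% and 5.2%. The simulation standard error near 5% is √(0.05 × 0.95/20,000), about 0.15 percentage points.

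**The case against.** The strongest reply is that a reader might infer that the planned test has an inflated type I error. The document does not support that. If STDP shifts both outcomes, the two changes really are correlated over all patients analysed (about 0.12 with both effects at 0.725 SD), and rejecting zero marginal correlation is then correct. The percentages above are the chance of detecting that marginal correlation; they become misleading only if a significant result is read as a within-arm link. The article also states no test or threshold for this analysis, so the 5% benchmark is supplied here. This objection stands, and it limits the point to interpretation.

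Second, the article does not say outright that the arms are pooled, and it refers to a statistical analysis plan that is not shown and may compute the coefficients by arm. The same section describes the secondary ANCOVA only as baseline-adjusted, although treatment must be in that model, so silence about arm is weak evidence. This stands as a caveat. It does not remove the point, because the method actually named has no arm term.

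Third, the pooled coefficient answers a legitimate question: whether patients whose peak VO₂ rises also feel better, whatever the cause. True, but the sentence does not say which question is meant, so the coefficient should be labelled.

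Fourth, the Discussion sentence says only that improvement may reflect such gains, and rests on a citation. No part of the article offers this correlation as its proof; that link is an inference about likely use.

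Finally, the SAQ effects are assumed, and the 0.725 SD comes from a cross-sectional comparison of patients with and without microvascular dysfunction, not from a treatment effect. The size could be much smaller.

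**Conclusion.** The point holds as a caution on method and interpretation. A plain coefficient pooled over arms cannot separate a shared treatment shift from a within-arm association.

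The size is conditional on pooling, on a peak VO₂ effect at the design value, and on a symptom effect that the document does not give. For symptom effects of 0.3 to 1.0 SD the spurious component of r is small in absolute terms (0.05 to 0.15). It is still enough to make a conventional 5% test significant well above one time in twenty, except at the lower end of that range. If the true effect on peak VO₂ is also modest, the problem largely disappears.

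The analysis is exploratory; the primary analysis, sample size and safety evaluation are untouched. This is a minor improvement worth making, not an error in the trial's main inference.

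**What to change.** In Statistical analysis, Secondary outcomes, or in the statistical analysis plan, specify a partial Pearson or Spearman correlation between the two changes, adjusted for treatment arm and reported with a 95% CI. Show the arm-specific coefficients alongside, so that a difference between arms is visible. The pooled coefficient may also be reported if it is labelled as marginal, that is, as including any shared effect of treatment.

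A regression of symptom change on change in peak VO₂ with arm and both baseline values is an optional further analysis. It conditions on more variables and is not equivalent to the arm-only partial correlation; it was not evaluated above.

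The cost is a sentence of text, one degree of freedom and no new data. With no treatment effect, power for a true within-arm correlation of 0.3 at 42 per arm is 79% with or without the adjustment. The one visible downside is a smaller coefficient when STDP affects both outcomes, which is the purpose of the change. As planned unblinding follows database lock and the trial is recruiting, this can be settled before any comparative result is seen.

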#### Missing data

Missing primary endpoint data at week 12 will be handled via multiple imputation under the missing-at-random assumption. Sensitivity analyses will include complete-case analysis and other prespecified approaches when needed, such as pattern-mixture models or conservative imputation methods.

All the statistical tests will be two-sided. The overall two-sided significance level for the primary endpoints will be set at *α* = 0.05 after adjustment for multiplicity. Analyses will be performed via SPSS (v26.0) and/or validated statistical software (e.g., SAS/R) as specified in the SAP.

#### Medication adherence analysis

Medication adherence will be assessed by structured interviews, medication diaries, and pill counts based on returned containers at each visit. Adherence will be calculated as (doses taken ÷ doses prescribed) ×100% and categorized as good (≥80%), moderate (50%–79%), or poor (<50%). Adherence summaries will be presented to the treatment group. Protocol-defined thresholds are used to guide counseling and reinforcement. Adherence will also be considered in sensitivity analyses, including per-protocol analyses excluding major protocol deviations and exploratory dose‒response analyses when appropriate. All adherence data will be recorded in the eCRF with audit trials.

### Nested diagnostic study: AI model development and validation

We will retrospectively collect dynamic stress MCE flash-replenishment sequences from participating centers, de-identify them, and transfer them to a central imaging core laboratory. To minimize interscanner and intersite variation while preserving replenishment kinetics, we apply a standardized preprocessing pipeline that includes speckle denoising with motion stabilization, contrast normalization with intensity scaling, frame alignment with temporal smoothing, and image resizing with pixel-level standardization. Two expert echocardiographers will assign quality labels to build a supervised image quality control module. A convolutional neural network (CNN) will then perform automated image quality classification and artifact detection, such as uneven illumination, attenuation (black apex), and motion blur. We will exclude low-quality frames according to predefined rules and apply artifact correction when feasible. Expert frame-by-frame annotations of endocardial and epicardial borders will serve as the reference to develop a temporally consistent segmentation model (e.g., temporal U-Net or ConvLSTM-U-Net) for stable myocardial tracking across frames. We will evaluate model performance using the Dice coefficient, Hausdorff distance, and temporal consistency metrics. From the segmented myocardium, we will generate pixel-level and segment-level time-intensity curves and fit them for perfusion quantification to derive A, *β*, MBF (A  ×  *β*), and area under the curve (AUC). When paired rest-stress data are available, we will calculate reserve indices, including *β* reserve and A  ×  *β* reserve/CFR. We will also extract radiomic texture features and acoustic features to describe spatial heterogeneity. We will perform feature selection using mutual information and LASSO to reduce redundancy and improve robustness. We will develop CMVD classification models mainly with random forest and XGBoost, and optimize hyperparameters via cross-validation. We will evaluate model performance on separate training, validation, and independent test datasets. External validation will be performed using an independent dataset collected from one participating site that was not used for model training or internal validation. The model's generalizability will be assessed by evaluating its performance on this separate dataset. The functional reference standards will include PET-derived flow reserve or expert-validated iMCE-CFR. Performance metrics will comprise accuracy, sensitivity, specificity, F1 score, and area under the receiver operating characteristic curve (AUC). We will use ROC analysis to assess discrimination, calibration curves to assess agreement between predicted and observed probabilities, and Bland-Altman analysis together with intraclass correlation coefficients to assess agreement between the AI-derived quantitative indices and iMCE outputs. Figure 2 shows the AI-based diagnostic workflow for coronary microvascular disease based on stress MCE.

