**Design:**

This is a prospective, multicenter, randomized, double-blind, placebo-controlled clinical trial with a nested diagnostic design. CMVD will be diagnosed by stress MCE, and eligibility will require evidence of reduced myocardial perfusion or perfusion defects. Eligible patients with CMVD will be randomized at a 1:1 ratio to receive STDP or a matched placebo for 12 weeks. The primary endpoint is the change in peak oxygen uptake (peak VO₂) measured by cardiopulmonary exercise testing (CPET). The secondary outcomes include other CPET indices, angina severity, quality of life, and circulating biomarkers. The nested diagnostic study uses retrospectively and prospectively collected MCE datasets to develop AI-based models for automated myocardial segmentation, perfusion curve analysis, and CMVD classification, with performance assessed against established reference standards.

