#### Quantitative assessment

Offline analysis will be performed via iMCE software (Narnar, China). The left ventricle was segmented according to the American Heart Association (AHA) 17-segment model. Standardized regions of interest (5 × 5 mm) will be placed within the myocardium, with motion tracking and manual adjustment when needed. The time‒intensity curves were fitted with the following equation:$$y(t)\;=\;A\;\times \;(1\text{-}e^{\wedge \;}(\text{-}\beta t))\;+\;B$$In this model, A represents microvascular blood volume, *β* represents microvascular flow velocity, and A×*β* estimates MBF (17). The CFR is calculated as the ratio of the stress MBF to the remaining MBF at the segmental level. The global CFR is obtained by averaging the segmental values. Interobserver and intraobserver variability will be assessed in a random 10% sample.

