
**Figure 2 F2:**
[figure not shown]
AI-augmented diagnostic workflow for coronary microvascular disease based on stress MCE. Dynamic stress MCE sequences acquired via high–mechanical index (high-MI) flash are first processed by a CNN-based module for image quality assessment, enabling artifact detection and classification. High-quality images are subsequently analyzed via a temporal deep learning model to achieve consistent myocardial segmentation across the cardiac cycle. The quantitative perfusion parameters, including the plateau intensity (A), replenishment rate (*β*), myocardial blood flow (MBF = A × *β*), and CFR, are derived from time–intensity curves. These features, together with radiomic descriptors, are integrated into machine learning models (e.g., random forest, XGBoost, and ResNet) for CMVD diagnosis and risk stratification. Model performance is evaluated via discrimination, calibration, and agreement metrics. MCE, myocardial contrast echocardiography; MI, mechanical index; CNN, convolutional neural network; MBF, myocardial blood flow; CFR, coronary flow reserve.

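### Where iMCE-CFR supplies the label, the AI classifier's accuracy and AUC show agreement with expert MCE reading, not independent detection of CMVD

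*Protocol article*

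**What the plan says.** **Inputs.** The section on AI model development derives A, β, MBF and area under the curve from the segmented myocardium, and adds: "When paired rest-stress data are available, we will calculate reserve indices", among them the A×β reserve, that is, CFR. The Figure 2 caption lists plateau intensity, replenishment rate, MBF "and CFR, are derived from time–intensity curves", and continues: "These features, together with radiomic descriptors, are integrated into machine learning models". The stated purpose of those models is CMVD diagnosis and risk stratification.

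**Reference.** The same section states: "The functional reference standards will include PET-derived flow reserve or expert-validated iMCE-CFR". The abstract describes the nested study as one "with performance assessed against established reference standards".

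**How iMCE-CFR is obtained.** Under Quantitative assessment: "Offline analysis will be performed via iMCE software (Narnar, China" [...]. Curves are fitted for A and β, MBF is A×β, and "The CFR is calculated as the ratio of the stress MBF to the remaining MBF at the segmental level". The remaining MBF is read here as resting MBF, in line with the Introduction's definition of the reserve index.

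**Metrics.** Accuracy, sensitivity, specificity, F1 and ROC AUC are planned, with calibration curves. Bland-Altman and intraclass correlation are planned separately for AI indices against iMCE outputs.

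**The concern.** A diagnostic accuracy study needs a reference that does not share its content with the test under evaluation. Here one of the two permitted references is the quantity that the classifier receives as a feature, or can approximate from its other features. When that reference supplies the label, a high AUC shows that two readings of MCE recordings agree. It does not show that either of them detects microvascular disease. Errors that affect the recording itself, such as attenuation or uneven opacification, move both readings in the same direction and are scored as correct.

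At stake is what the nested study can conclude. The Introduction sets out to develop and validate a tool for CMVD detection and stratification. Followed as written, the plan could report replication of the iMCE software as accuracy for CMVD.

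**Working it through.** The article gives no sample size, target AUC or expected accuracy for the nested study, so there is no stated figure to reproduce. The check is a trace through the text, followed by an illustration.

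**1. Input against reference.** The AI feature is the stress/rest ratio of A×β from replenishment curves (AI section; Figure 2 caption). The reference is also the stress/rest ratio of A×β from replenishment curves (Quantitative assessment). Quantity, formula and modality are the same. Segmentation and region placement differ.

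**2. Same examinations?** The text does not say so outright. However, Bland-Altman and intraclass correlation against iMCE outputs need both readings on the same patients, and the follow-up section gives trial participants one stress MCE that is not repeated. Use of the same examinations is therefore a strong inference.

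**3. Is there a rule that separates the two?** The article has no rule that assigns a reference to a dataset, requires PET in the test or external-site set, or limits iMCE-referenced results to agreement.

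**4. Illustration. All inputs are assumed; none comes from the documents.** Let the examination-level CFR signal have variance 1. A share r is true flow reserve, and 1 − r is error common to both readings. The AI and iMCE readings each add their own independent error of variance e. All cuts are at the median. Then

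- correlation of AI with iMCE: ρ = 1/(1 + e)
- correlation of AI with truth: ρ = √(r/(1 + e))
- proportion correctly classified: 1/2 + arcsin(ρ)/π

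Against iMCE with e = 0.05: ρ = 1/1.05 = 0.952, and accuracy = 0.5 + 1.261/3.142 = 0.901. With e = 0.20: ρ = 0.833, and accuracy = 0.5 + 0.985/3.142 = 0.814. The share r does not enter. Against truth with r = 0.5 and e = 0.05: ρ = √(0.5/1.05) = 0.690, and accuracy = 0.5 + 0.762/3.142 = 0.742.

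AUC from 200,000 draws:

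| r | vs iMCE, e = 0.05 | vs truth, e = 0.05 | vs iMCE, e = 0.20 | vs truth, e = 0.20 |
|---|---|---|---|---|
| 0 | 0.970 | 0.500 | 0.901 | 0.502 |
| 0.3 | 0.970 | 0.746 | 0.902 | 0.732 |
| 0.5 | 0.970 | 0.825 | 0.902 | 0.803 |
| 0.7 | 0.970 | 0.891 | 0.901 | 0.862 |
| 0.9 | 0.971 | 0.955 | 0.901 | 0.918 |

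The iMCE columns are flat in r, so the iMCE-referenced AUC carries no information on how valid MCE is. The last row also shows that the gap is not fixed in size or even in sign: with near-perfect MCE and large reading error, AUC against truth is slightly the higher (0.918 against 0.901).

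A second set of assumptions (log-normal CFR, median 2.2, log-SD 0.3, cut at 2.0, AI reading equal to iMCE with 10% error) gives 0.969 against iMCE. Against PET it gives 0.677, 0.764 and 0.864 at log correlations of 0.4, 0.6 and 0.8, which are gaps of 0.292, 0.205 and 0.105.

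**The case against.** Much of the case on the other side stands.

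- **Agreement with expert iMCE is a proper target for automation.** The article wants the AI to reduce observer variability and operator dependence, and for that aim expert iMCE is the natural comparator. The trial also uses CFR below 2.0 on stress MCE as its own diagnostic criterion. This defends the comparison, but not presenting it as accuracy for CMVD.
- **The two readings are not one number.** iMCE uses 5 × 5 mm regions with manual adjustment, whereas the AI uses pixel-level and segment-level curves. CFR is an input only with paired data, and feature selection follows. Agreement is therefore not guaranteed, and calling the whole evaluation circular goes too far. Cases scored against PET are not affected.
- **A reader might infer from Table 1 that no PET reference will exist.** The visit schedule lists no PET, but it says nothing about the retrospectively collected recordings. Randomised participants are also required to have CFR below 2.0, so they alone could hardly supply the non-diseased cases that specificity and AUC need.
- **A reader might infer that PET and iMCE labels will be pooled in one AUC.** The wording permits that but does not state it.
- **A condensed article may leave the assignment of references to a fuller document.** That is fair for the detail. The point rests on what the article does fix: the inputs, the permitted reference and the accuracy metrics.

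**Conclusion.** The point holds for cases labelled by iMCE-CFR. For those, the classification metrics are subject to incorporation bias and measure how well the AI reproduces expert MCE reading. External validation at one site does not remove this if its label is also iMCE-CFR.

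The size cannot be determined from the documents. It might be tempting to quote an AUC overstatement of about 0.11 to 0.29, but that range comes wholly from an assumed CFR distribution, reading error and MCE-PET correlation. The simulations show only that the iMCE-referenced AUC does not respond to the validity of MCE. The conclusion rests on one inference, that both readings come from the same examinations, which the planned agreement analysis makes very probable.

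The stronger reading, that the nested study cannot validate the tool at all, is not supported: PET is a permitted reference, and agreement with experts answers the automation aim. Randomisation, the peak VO₂ endpoint and its analysis are untouched. The article also describes its expected yield as pilot data and asks for further external validation of the AI model. This is a should-fix, to be settled before model evaluation.

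**What to change.** In the section on AI model development and validation:

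1. Report results against PET-derived flow reserve and against iMCE-CFR separately, and never combine the two in one AUC.
2. Base any claim of diagnostic accuracy for CMVD on PET-referenced cases only, and state how many there are in each dataset.
3. Describe every result against iMCE-CFR, including classification metrics and those from the external site, as agreement with or automation of expert MCE reading. Place them next to the Bland-Altman and intraclass correlation results already planned.

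Removing MBF, reserve and CFR from the classifier inputs is no substitute. A and β would remain, and since MBF = A×β the model could largely rebuild what was removed.

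The text change is small. The real cost is that the PET-referenced subset may be small or absent, which means wider intervals or a claim limited to automation of MCE reading.
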